•Eligibility at time of recruitment (12% continuation).

•Consent at time of recruitment (30% continuation).

•Continuity through study (43% continuation).

•Study-designed attrition (estimated 10% attrition).

•Increased awareness of the study purpose, through the previous successful relationship established between the research team and the Royal Adelaide Hospital (RAH) staff, regarding awareness of detecting the risk of FD (estimated as improving the capture rate of eligible individuals by 10%).

Thus, to provide a continuing sample of 200 total subjects (with high and low SF12-MCS) at three months follow-up, we require a continuing eligible sample at the one-month assessment point of 220+ individuals; therefore we require a sample of 570 eligible consenting individuals recruited on discharge from ED. Based on previous experience, this will take 14 weeks at the participating hospital.

For the nested RCT, we also took into account an assumed rate of refusal for the intervention of 1:10 individuals who are offered it. This figure is based on pilot feedback from ECH, the intervention provider. We will address a potential loss of power in our intervention arm, which would occur if eligible subjects refused, by replacing every second refuser in the intervention group with an individual randomly selected from the control group for the RCT, who was recruited at the same time as the refuser. By replacing 1:2 refusers (as opposed to 1:1), this retains the balance in the two intervention arms. We will also analyze the characteristics of the refusers qualitatively, to identify whether they are different from the individuals who agreed to participate in the intervention.

Intention to treat analysis will be used when data are missing. However, every effort will be made to minimize missing data. For instance when subjects are unable to be contacted at the agreed time for any one data collection point, we will note their data as missing; however, reasons for loss to follow-up will be sought by making further contact with the subject. If possible, replacement telephone interviews will be conducted within days of the missed appointment, to provide the missing information. When subjects provide some data during the telephone interview, but not all, reasons for missing information will be recorded, to determine the appropriateness of using ‘carry-forward last known value’.

### Analysis of data from Studies 1 and 2

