The three study cohorts will be assessed at time of allocation into a study arm (one-month after recruitment) for homogeneity in key socio-demographic characteristics and immutable factors (for example, gender, age, schooling, postcode, diagnosis) and all outcome measures (including the percentage of ‘frequent flyers’ in each arm). We previously reported this as one or more ED contacts per month over the preceding 12 months [33,34].

Change over time in each outcome measure will be calculated using repeated measures analysis of variance (ANOVA) models, with study contact point, cohort (1, 2, or 3) and key demographic features as independent variables. Partial Least Squares (PLS) models using pathway analysis will be applied to the multiple outcome, immutable and mutable independent variables at each time point, to determine different spatial arrangements and the significant factors which impact on data clusters.

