### Hypotheses

As shown in Figure 2, our hypothese are:

1. The observed cohort will not demonstrate FD over the following 12 months in any FD measure.

2. The low SF12-MCS, no treatment cohort will demonstrate significant FD in any one or more outcome measures, taken over the next three months, when compared to their baseline recruitment status.

3. The low SF12-MCS, intervention cohort will show no FD (comparable findings to the observed cohort) over the next 12 months.

4. Additionally, those individuals in the low SF12-MCS, no treatment cohort who demonstrate significant FD at three months follow-up, and who access ‘rescue’ intervention (see Section on Ethics), will show an attenuated rate of FD over the following twelve months, compared with the rate they exhibited in the first three months.

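### Intention to treat is misdescribed as a missing-data device, carry-forward is left open on a declining outcome, and the named repeated measures ANOVA sits badly with incomplete series

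*Protocol article*

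**What the plan says.** All the missing-data rules stand in one paragraph near the end of Sample size considerations. It opens: "Intention to treat analysis will be used when data are missing". It then separates two situations.

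- **A contact is missed.** The article says "we will note their data as missing", that reasons will be sought, and that, if possible, "replacement telephone interviews will be conducted within days of the missed appointment, to provide the missing information". No imputation is mentioned here.
- **An interview is only partly completed.** "When subjects provide some data during the telephone interview, but not all", the "reasons for missing information will be recorded, to determine the appropriateness of using" carry-forward of the last known value. No criterion for appropriateness is given.

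The model is named in Analysis of data from Studies 1 and 2: "Change over time in each outcome measure will be calculated using repeated measures analysis of variance (ANOVA) models", with contact point, cohort and demographic features as independent variables. How a participant with an incomplete series enters it is not said.

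The expected direction of the outcome is given under Hypotheses: "The low SF12-MCS, no treatment cohort will demonstrate significant FD in any one or more outcome measures", while the intervention cohort is expected to show none over 12 months.

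**The concern.** Three statements do not fit together.

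1. Intention to treat is a rule about who is analysed and in which arm. It applies with complete data too, and it says nothing about how a missing value is handled. Invoking it only when data are missing leaves both questions open: whether participants are analysed as randomised, and how gaps are dealt with.
2. The trial's outcome is decline. A value carried forward from an earlier contact records no change since then, which is what the intervention is hoped to achieve. Deciding whether to use it after seeing the reasons, with no rule, leaves an avoidable choice until the data are in.
3. A classical repeated measures ANOVA needs a full series from each participant. Used on data where missed contacts stay missing, it becomes an analysis of completers, which is not intention to treat in any sense. It also assumes sphericity, which is doubtful for contacts at 0, 1, 4, 7 and 13 months.

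At stake are the validity of the randomised comparison if those who miss calls differ from those who do not, and its power.

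**Working it through.** **Loss the plan itself expects.** Sample size considerations asks for 220+ people at the one-month assessment in order to have 200 at three months after randomisation.

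- Loss by the first post-randomisation contact: (220 − 200)/220 = 9.1%. This covers high and low SF12-MCS groups together and is not split by arm. Loss after that contact is not quantified.
- Low SF12-MCS half, taking an even split at the median: 220/2 = 110 randomised, 55 per arm.

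**Where the 43% continuation belongs.** 570 × 0.43 × 0.90 = 220.6, which reproduces the 220+ at one month. Despite its label, the figure is used up before randomisation.

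**Complete series under classical ANOVA.** Assumption: each of the three post-randomisation contacts is missed by 10%, independently. The 10% is close to the 9.1% above, but the article gives no rate per contact.

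- Complete series: 0.9³ = 0.729, and 0.729 × 110 = 80 people, about 40 per arm.
- Available at any one contact: 0.9 × 110 = 99.

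A model that uses all available contacts would therefore work with about 99 people at each contact, against 80 throughout.

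**What that could cost in power.** The article gives 50 per arm for a 1.2-point iADL difference at three months, 80% power and 5% alpha, but no SD. Assuming a two-sided test and the normal approximation:

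- Implied SD = 1.2 × √(50/2) / (1.960 + 0.842) = 2.14.
- With 40 per arm: SE = 2.14 × √(2/40) = 0.479; 1.2/0.479 − 1.960 = 0.545; power about 71%, against 80% planned.

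This treats the comparison as a two-sample contrast at three months, so it is an illustration of scale.

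**Carry-forward.** Suppose a fraction m of an arm has a value carried forward over an interval in which that arm truly declines by δ. The arm's decline is then understated by m × δ, and the contrast shifts towards the intervention by (m × δ in intervention) − (m × δ in control).

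- Equal decline and equal fractions: the shift is zero.
- Equal decline, more values carried in one arm: the shift favours that arm.
- Controls decline by 1.2, intervention arm by 0 (an assumption in line with the hypotheses): with 10% of control values carried, the difference is 0.9 × 1.2 = 1.08; with 30%, 0.7 × 1.2 = 0.84. The shift is against the intervention.

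The article gives no value for m in either arm, so neither size nor sign can be fixed.

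**The case against.** The strongest reply is that this is loose wording in a condensed article. Covariance structure, sphericity correction, estimation method and sensitivity analyses commonly belong in an analysis plan that is not shown. The article does not say that its ANOVA deletes incomplete series, and the 10% per contact is not its figure. The last two points stand, which is why the 73% and the 71% power are conditional. The absence of modelling detail is not in itself the complaint. But the intention-to-treat sentence, carry-forward as an option and the ANOVA are things the article states, and the first is stated wrongly.

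A reader might also infer more than the text supports:

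- **That decline in dropouts is frozen by carry-forward.** It is not planned. Missed contacts are left missing; carry-forward is considered only for partly completed interviews, and conditionally.
- **That 43% continuation means heavy loss from the trial arms.** The arithmetic places it before randomisation, so it cannot create a difference between arms.
- **That refusal by 1 in 10 is data loss in one arm.** It is refusal of the intervention. The article does not say that refusers stop the outcome calls.
- **That carry-forward would favour the intervention by a calculable amount.** The sign depends on decline and fraction carried in each arm. A 12-month bias built on assumed dropout also cannot be set against a 1.2-point target that applies at three months.

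**Conclusion.** The point holds in this form: intention to treat is misdefined, analysis as randomised is nowhere stated, carry-forward is left as an unruled option on a declining outcome, and the named model in its classical form would conflict with intention to treat.

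The size that rests on the plan's own numbers is about 9% loss by the first post-randomisation contact. The 73% with complete series rests on an assumed 10% missed independently at each of three contacts, and the fall in power from 80% to about 71% rests also on an SD implied by the stated sample size. No magnitude can be given for carry-forward. The wording should be changed before analysis; nothing here shows that the trial cannot answer its question.

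**What to change.** 1. Replace the intention-to-treat sentence with a statement that all randomised participants are analysed in the arm to which they were randomised, whether or not data are missing.
2. For the comparison of the two randomised arms, replace repeated measures ANOVA with a likelihood-based mixed model using all available contacts: contact as a category, unstructured covariance, arm-by-contact interaction, and the one-month value as covariate. Counts and categorical outcomes need a counterpart suited to their type.
3. Remove carry-forward, including for partly completed interviews. An outcome that cannot be scored is left missing at that contact.
4. Because the mixed model takes data as missing at random, add a sensitivity analysis that assumes worse outcomes in those lost.

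Keep the replacement interviews and the recording of reasons. The cost is analysis wording only: no added participants, contacts or measures.

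The same section's replacement of some refusers by people from the control group also bears on analysis as randomised. It is a separate matter, to be settled alongside item 1.

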## Study aim

1. To determine whether an individualized early intervention for community-dwelling older people with poor mental component quality of life scores measured one month after discharge directly from a hospital emergency department (ED), reduces their likelihood and/or rate, of functional decline (FD) over the next twelve months.

2. To demonstrate that:

a. Incipient FD in an older person can be identified within four weeks of discharge from an ED presentation for a minor health event, using lower than median mental component quality of life scores; and

a. Engaging these older people early, into a person-centered home-based intervention, arrests or reduces the rate of FD over the next 12 months.

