### Study 2: nested RCT

#### Subject selection and randomization

All participants in Study 1 will be stratified at one-month telephone follow-up into low and high scores on the MCS domain of the SF-12, (SF12-MCS), using the median cut point. We previously reported this as a transformed score of 55 [37], which is comparable to the same age-gender population SF-12 norms [41]. The nested RCT will be conducted involving only the subjects with lower than median SF12-MCS scores at this time point (Figure 1).

An independent trials office will randomize these subjects using a computer generated random number series, into an individualized person-centered community-based intervention, or ‘usual care’ which reflects no intervention. It is unlikely that any intervention would normally be offered to this population as it is not current practice to screen people for low mental component quality of life scores after an ED contact.

Considering Studies 1 and 2, there are three study cohorts (Figure 1):

•Subjects with SF12-MCS scores ≥55, who will be observed only, for 13 months after recruitment (12 months after the one month SF12 scores are taken) (the observed cohort)

•Subjects with SF12-MCS scores <55, from which two RCT groups will be allocated one month after recruitment, randomized into

•Intervention specifically tailored to address the individual’s problems, concerns, and goals (low SF12-MCS, intervention cohort)

•No treatment (low SF12-MCS, no treatment cohort).

Outcome measures for the two RCT groups will be taken at three-, six- and twelve-month time points after randomization (four, seven and thirteen months post-recruitment).

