### Sample size considerations

To date, there is scant research that has established the effectiveness of any community-based person-centered intervention program that alerts older people who are on the cusp of FD to impending FD and provides means to assist and support them. We drew the likely effectiveness of the proposed intervention program from research on early intervention programs for at-risk older people who are in hospital or rehabilitation units. This included an Australian study [47] (significant improvement in goals and functioning) and a Dutch study [48] (effect size 0.25). We acknowledge that this research may not be readily generalizable to estimate effectiveness of the intervention in our reference population; however, it is the best available evidence for sample size calculation.

Our nested RCT study sample size was further calculated on minimal differences in iADLs and SF12 scores, expected at three-month follow-up from our pilot data [37]. These estimates are based on the three-month follow-up distributions for iADLs and SF-12. Parameters of power were set at π = 80% (1-β), with α = 5%. For iADLs, we identified that a minimum absolute effect size of 1.2 would be needed for participants to have dropped by at most 1 point on the Lawton scale (the Lawton definition of FD requires a drop of 2+ points on the scale). Thus, a minimum sample size of N_IADL_ = 50 per RCT cohort would be required (total 100). For the MCS domain of SF-12, a minimum absolute effect size of 4.3 would need to be observed, to put all scores above or equal to the median value, giving sample size of N_MCS_ = 30 per RCT cohort (total 60). Similarly for the PCS domain of SF-12, the minimum absolute effect size of 12.2 gives a sample size of N_PCS_ = 6 per RCT cohort (total 12). We require significance to be determined both clinically and statistically, so over-sampling is not of concern and, therefore, we choose the highest sample size (N_IADL_) of N = 50 per RCT cohort (100 total) at three months RCT follow-up (four months from ED recruitment). Thus, our continuing RCT sample at three months will reflect 100 individuals with low SF12-MCS (randomized 50 each into intervention and control arms), and 100 individuals with high SF12-MCS who will simply be followed-up.

To provide the nested RCT cohort sample, there are specific considerations which will influence the number of individuals invited to participate in Study 1:

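### No single outcome and time point decides intervention versus no treatment: three outcomes are sized at an unsplit 5%, each measure gets its own model, and none is named as primary.

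*Protocol article*

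**What the plan says.** - **Aim (Study aim, item 1).** The programme is to be judged on whether it "reduces their likelihood and/or rate, of functional decline (FD) over the next twelve months". Two kinds of result would satisfy this, and no instrument is named.
- **Sizing (Sample size considerations).** "Our nested RCT study sample size was further calculated on minimal differences in iADLs and SF12 scores, expected at three-month follow-up". One set of operating figures serves all three calculations: "Parameters of power were set at π = 80% (1-β), with α = 5" per cent. For iADL, "a minimum absolute effect size of 1.2 would be needed for participants to have dropped by at most 1 point on the Lawton scale", which gives 50 per arm. SF12-MCS (difference 4.3) gives 30 per arm and SF12-PCS (difference 12.2) gives 6. The largest is adopted. Nothing says that iADL therefore decides the trial.
- **Visits (Subject selection and randomization).** "Outcome measures for the two RCT groups will be taken at three-, six- and twelve-month time points after randomization".
- **Measures (Outcome measures, Table 1).** There are 13 rows, or 14 scores if SF12 is split into MCS and PCS as in the sizing.
- **Definition of decline (Study 1 analysis).** Eleven criteria are assessed at each time point, with no rule for combining them.
- **Analysis (Analysis of data from Studies 1 and 2).** "Change over time in each outcome measure will be calculated using repeated measures analysis of variance (ANOVA) models", with contact point, the three cohorts and demographic features as independent variables. Partial least squares models follow. No test level is given.
- **Hypotheses.** Hypothesis 2 says that the untreated low-MCS cohort "will demonstrate significant FD in any one or more outcome measures", relative to its own recruitment status. Hypothesis 3 says that the intervention cohort will show no decline, comparable to the observed cohort. Neither names an outcome.

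**The concern.** The 5% behind the sample size protects one prespecified comparison, and this text does not say which one. The candidates can disagree: MCS may respond to socialisation or counselling while iADL does not, or a three-month gain may be gone by twelve months. Under Aim 1 as worded, any of these could be presented as success, because functional decline is never reduced to a single endpoint and the sizing horizon (three months) differs from the aim's (twelve months).

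This is more than detail left to an analysis plan. The primary outcome gives the sample size its meaning, and the article states several candidates and two horizons without choosing. An analysis plan could pick one test, but the aims and hypotheses would still allow a claim resting on another.

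**Working it through.** **1. The stated sample sizes.** For two means, n per arm = 2(SD/d)²(z_α + z_power)². The article gives d and n but no SD, so the formula can only be solved backwards: SD = d√(n/2)/(z_α + z_power), with 1.960 + 0.842 = 2.802 for two-sided 5% and 80% power.

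| Outcome | d | n per arm | Implied SD, two-sided | Implied SD, one-sided |
|---|---|---|---|---|
| iADL | 1.2 | 50 | 2.14 | 2.41 |
| SF12-MCS | 4.3 | 30 | 5.94 | 6.70 |
| SF12-PCS | 12.2 | 6 | 7.54 | 8.50 |

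The three figures are compatible with a full 5% for each outcome. Without an SD this is a consistency check, not an independent reproduction.

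**2. Chance of at least one false-positive arm difference, programme inert.** Assume one test per measure, each at unadjusted two-sided 5% (c = 1.96). The article gives no correlations, so a common correlation ρ is assumed.

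- Independent measures: 1 − 0.95^k. For k = 3, 1 − 0.857 = 14.3%. For k = 13, 1 − 0.513 = 48.7%.
- Correlated measures: 1 − ∫φ(x)[Φ((c − √ρ·x)/√(1−ρ)) − Φ((−c − √ρ·x)/√(1−ρ))]^k dx, integrated numerically.
- Benefit direction only: each test has a 2.5% chance. For independent measures 1 − 0.975^13 = 28.0%. Otherwise use the same integral with only the upper limit.

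| Tests | ρ = 0 | 0.3 | 0.5 | 0.7 | 0.8 |
|---|---|---|---|---|---|
| 3 sized outcomes, either direction | 14.3% | 13.6% | 12.5% | 10.9% | 9.8% |
| 13 measures, either direction | 48.7% | 41.8% | 33.4% | 24.1% | 19.2% |
| 13 measures, benefit only | 28.0% | 21.4% | 16.7% | 12.0% | 9.6% |

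The count of 13 is an upper reading of Table 1. With k = 11, one test for each decline criterion, the same formulas give 43% at ρ = 0, 30% at 0.5 and 18% at 0.8 in either direction. The conclusion does not depend on the exact count.

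**3. After the fix.** One prespecified outcome, contrast and time point returns the error rate to 5%. N = 50 per arm stands if that outcome is iADL at three months.

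**4. The alternative of keeping every outcome confirmatory.** Take Bonferroni at the implied iADL SD of 2.14:

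- Three outcomes (α = 0.05/3 = 0.0167) need 67 per arm. Power at 50 per arm falls to 66%.
- Thirteen outcomes (α = 0.05/13 = 0.0038) need 89 per arm. Power at 50 per arm falls to 46%.

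**The case against.** The best defence is that the article already ties N to iADL at three months, so only a label is missing, and that a full protocol, an analysis plan or the registry entry may supply it. That is possible, and the fix allows for it. But iADL was taken because it gave the largest n, which is not the same as making it decisive, and the aims and hypotheses would still need to be aligned.

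Several stronger readings are tempting and should not be made.

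- **All 13 measures are tested at full 5%.** A reader might infer this. The 5% is stated only for the sizing; for the analyses it is inferred from the absence of any adjustment.
- **A one-in-three false-positive risk.** The 33% needs 13 single tests and a correlation of 0.5, neither of which is in the article. It also counts results against the programme, which could not support a claim of benefit; the benefit-only figure at 0.5 is 17%.
- **Hypothesis 2 as the success rule.** Its any-one-or-more wording compares the untreated cohort with its own recruitment status. It shows how loosely decline is judged, but it is not the between-arm rule. Hypothesis 3, read literally, is closer to requiring no decline on every measure.
- **Multiplying by three visits.** The analysis section describes repeated measures models with contact point as a factor, not separate arm tests at each visit.
- **All 13 rows are outcomes.** The Outcome measures section says that Table 1 also records mutable independent variables, so some rows may not be outcomes.

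The sample size section also asks for clinical as well as statistical significance. If that means the minimum differences must actually be observed, false positives on the sized outcomes become rare. At 50 per arm the iADL difference sits at z = 2.80 (p about 0.005), and MCS at 2.80 × √(50/30) = 3.62. That is one reading, however, and it gives no threshold for the between-arm difference on the measures that were not sized.

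**Conclusion.** The concern holds in this form: the article fixes no outcome and time point that decides intervention versus no treatment, and its aims leave room to claim success on whichever measure is favourable. If measures are tested at an unadjusted two-sided 5%, the chance of at least one false-positive arm difference is about 10% to 14% for the three sized outcomes and about 19% to 49% for 13 measures (correlations 0.8 to 0). In the benefit direction only, it is about 10% to 28% for 13 measures, against 2.5%. The test level, the correlations and the count of 13 are assumptions. Even the narrowest of these cases, three outcomes at correlation 0.8, is about twice the nominal rate. The figures show scale; the defect is the missing choice, which does not depend on them.

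**What to change.** In the sample size and analysis sections, name one deciding test: iADL total score, intervention versus no treatment as randomised, at three months after randomisation, two-sided 5%. That outcome and time already set N = 50 per arm.

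Treat every other measure and time point, and the partial least squares models, as secondary or exploratory, reported with estimates and 95% confidence intervals, unless a fixed testing order is written down before unblinding. The content of such an order is the sponsor's choice.

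Reword the Study aim and Hypotheses so that significance on another measure alone does not support a claim of effectiveness. If the full protocol already names a primary outcome, align these sections with it instead.

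The cost is wording only: no extra participants, visits or data. The real downside is that a result confined to another measure, or to twelve months, is no longer confirmatory. This matters because Aim 1 looks to twelve months and programmes can run to fourteen weeks, past the three-month visit. If the sponsor prefers twelve months as the deciding time, the sample size has to be justified for that time, since the present one rests on three-month distributions.

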### Study 1 analysis

FD will be assessed as change from baseline at each time point as:

•One or more falls increase from the baseline rate

•More than one event of hospitalization, or ED presentation, from the baseline rate

•Decrease of one point in any item of the ADL instrument [18], or

•Decrease of 2+ points from baseline total iADL score [19], or any decrease in baseline score in the domains of home activities, doing laundry, shopping and getting places (we previously reported these domains as critical to functional independence) [37]

•Scores decreasing from above median at baseline in either physical or mental domain, to below median in the SF12 [41,42]

•Any decrease in AQoL_4D (in the manner recently described for chronic obstructive pulmonary disease (COPD))[44]

•Change to a more assistive gait aid (for example, a one point stick to a four-pronged stick)

•Change in living arrangements to more supported care

•Increased carer involvement

•Greater type and frequency of use of formal community services or informal supports

•More frequent GP attendances.

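### The aim is to reduce the likelihood of functional decline, defined by person-level thresholds, but no stated analysis compares the proportion declining between the randomised arms

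*Protocol article*

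**What the plan says.** **Aim.** Under *Study aim*, the first question is whether the intervention "reduces their likelihood and/or rate, of functional decline (FD) over the next twelve months".

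**Definition of FD.** *Study 1 analysis* opens its list of criteria with "FD will be assessed as change from baseline at each time point as". There are eleven criteria, and most are met or not met by an individual. The iADL criterion reads "Decrease of 2+ points from baseline total iADL score [19], or any decrease in baseline score in the domains of home activities", continuing to three further domains. Others are a one-point fall on any ADL item, a more assistive gait aid and a move to more supported living. No rule says how the eleven combine.

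**FD as a state of individuals.** The fourth item under *Hypotheses* selects "those individuals in the low SF12-MCS, no treatment cohort who demonstrate significant FD at three months follow-up". *Ethical issues* likewise speaks of any participant identified as showing possible FD.

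**Analysis.** *Analysis of data from Studies 1 and 2* states: "Change over time in each outcome measure will be calculated using repeated measures analysis of variance (ANOVA) models", with contact point, cohort and demographics as independent variables. It adds: "Partial Least Squares (PLS) models using pathway analysis will be applied to the multiple outcome, immutable and mutable independent variables at each time point". No other outcome analysis is named.

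**Power.** *Sample size considerations* sets 80% power and 5% alpha. It applies them to absolute score differences: 1.2 for iADL (50 per arm), 4.3 for the SF-12 mental score (30 per arm) and 12.2 for the physical score (6 per arm). The 1.2 is justified by reference to the 2+ point Lawton definition of FD.

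**The concern.** A mean trajectory and a threshold event are different quantities and can give different answers. Suppose all 50 people in one arm lose 1 iADL point: the mean falls by 1.0 and nobody has a 2+ point drop in the total. Suppose instead that 25 of 50 lose 2 points and 25 lose none: the mean again falls by 25 × 2 / 50 = 1.0, but half the arm has declined by that criterion. ANOVA on the score does not separate these cases. The question about likelihood turns on exactly that difference.

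At stake is the wording of the main conclusion. If the plan is followed as written, a difference in means may be reported as FD prevented, without a risk difference for FD between the randomised arms. For measures with no natural mean, or with counts gathered over different periods, the named model would give estimates that are hard to interpret.

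**Working it through.** **1. Do the stated analyses reach the stated aim?**

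| Part of the plan | Quantity |
|---|---|
| Study aim, likelihood | Proportion of people with FD |
| Study aim, rate | Speed of change |
| Study 1 analysis | Thresholds per person, per contact |
| Hypotheses, item 4 | Individuals who show FD |
| Sample size | Difference in scores |
| Repeated measures ANOVA | Mean change in each measure |
| PLS path models | Factors and data clusters across many variables |

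ANOVA matches the rate row. Neither method compares the proportion with FD between the intervention and no-treatment arms.

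**2. Does ANOVA fit each measure?** Table 1 includes gait aid type and living arrangements, which are categories. Falls are counted over 12 months at baseline, then over 1, 3, 3 and 6 months. Hospitalisations are counted over 6, 1, 3, 3 and 6 months. A raw count over 6 months cannot be compared directly with one over 3 months.

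**3. What does the 80% refer to?** The protocol gives no SD, so 50 per arm cannot be reproduced independently. The SD that it implies can be back-solved from n = 2 × SD² × (z for alpha + z for power)² / difference²:

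- Two-sided 5% (sidedness is not stated): SD = 1.2 × √(50/2) / (1.960 + 0.842) = 6.0 / 2.802 = 2.14. The standardised difference is 1.2 / 2.14 = 0.56.
- One-sided 5%: SD = 6.0 / (1.645 + 0.842) = 2.41.
- Reading 1.2 as a standardised effect would need only 11 per arm.

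The 50 is thus consistent with comparing means in scale points. No FD proportion enters it.

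**4. Illustration: the same shift scored as one iADL cut.** Assumptions: normal change scores, SD 2.14 in both arms, two-sided 5%, 50 per arm. The treated proportion is pT = Φ(Φ⁻¹(pC) − 0.56). Power is Φ[(pC − pT − 1.96 × SE0) / SE1], where SE0 is the pooled and SE1 the unpooled standard error.

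- pC = 50%: pT = Φ(−0.56) = 28.8%. SE0 = 0.0977 and SE1 = 0.0954. Power = Φ[(0.212 − 0.1915) / 0.0954] = Φ(0.21), about 59%. About 82 per arm would give 80%.
- pC = 30%: pT = Φ(−0.524 − 0.560) = 13.9%. SE0 = 0.0828 and SE1 = 0.0812. Power = Φ[(0.161 − 0.1623) / 0.0812] = Φ(−0.02), about 49%. About 103 per arm would give 80%.

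The 30% and 50% are borrowed from *Pilot work underpinning this protocol*, where they are likelihoods of FD at discharge. They serve here only as assumed control rates.

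**5. Sensitivity.** Fixing the cut at a 2-point drop (or at 1.5, to allow for whole-number scores) and letting the control mean drop run from 0.6 to 3 points gives power of 46–60% and 80–113 per arm.

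**6. What 50 per arm can detect as an event.** 80% power is reached if 50% falls to about 23%, or 30% to about 8%.

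**The case against.** **This is a condensed article, and an analysis plan may add an event analysis.** That is fair as far as silence goes, and the absence of a fully specified secondary model is not the point. But the article does not leave the method open. It names a mean-based model for each outcome measure, beside an aim and a definition framed as events.

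**The aim says and/or, and the hypotheses are largely about cohorts.** This stands in part. ANOVA with contact point and cohort does address rate, and the first three hypotheses can be read as trajectories. The likelihood part remains uncovered.

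**FD is not ignored.** This also stands. A reader might infer that FD is never analysed. The protocol does commit to assessing the FD criteria in every participant; what is missing is the comparison of the result between randomised arms.

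**The power claim is not false.** A reader might infer that the protocol promises 80% power for FD. It does not: it ties the 80% to iADL and SF-12 score differences only.

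**The 50–60% does not describe FD as listed.** Correct. It describes one cut on one score. The list also includes, for example, any fall in AQoL, more GP attendances and any loss in four iADL domains. With no combining rule, neither the control rate nor the effect of a 1.2-point shift on the combined event is known. The back-solved SD is used for change scores, although the protocol refers to follow-up distributions.

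**Gait aid and living arrangements can be ordered.** True, since the criteria speak of more assistive aids and more supported care. Table 1 also mixes outcomes with mutable independent variables, so it is not certain that ANOVA is meant for each row. Ordering argues for an ordinal model rather than a comparison of means.

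**Conclusion.** The concern holds in a limited form. FD is set out by person-level thresholds and its likelihood is part of the first aim, yet the stated analyses contain no comparison of the FD proportion between the randomised arms. ANOVA serves only the rate part, and it is a poor choice for the categorical measures and for counts over unequal windows. This rests on the text and needs no numerical assumption.

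The documents do not support calling the trial underpowered for FD. The illustration of about 50–60% applies to a single 2+ point iADL cut. It depends on a back-solved SD of about 2.1, normal change scores, a two-sided 5% test and assumed control rates of 30–50%. A larger effect on the event, such as 50% falling to 23%, would still have 80% power. What does follow is that the stated 80% cannot be carried over from the mean score to the event.

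**What to change.** 1. Keep the iADL total as the continuous analysis for rate, and state that the 80% power at 50 per arm refers to the mean iADL score difference only.
2. For likelihood, define an FD event and compare it between the two randomised arms at each post-randomisation contact (three, six and twelve months). Use repeated-measures logistic or log-binomial regression and report a risk difference with its confidence interval. At minimum the event should be "Decrease of 2+ points from baseline total iADL score", the threshold that the sample size section itself invokes. If more criteria are included, state the rule that combines them.
3. Use ordinal or multinomial models for gait aid and living arrangements, and count models with an offset for window length for falls and hospitalisations.
4. If power for the event is mentioned, give it for the single iADL cut with its assumptions, and give no figure for the full list of criteria.

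The cost is revised wording and a few standard models on data already being collected, with no new patients or visits. The one unwelcome consequence is a less favourable power statement for the event.
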